## Abstract

**Background:**

Coordination of care, especially after a patient experiences an acute care event, is a challenge for many health systems. Event notification is a form of health information exchange (HIE) which has the potential to support care coordination by alerting primary care providers when a patient experiences an acute care event. While promising, there exists little evidence on the impact of event notification in support of reengagement into primary care. The objectives of this study are to 1) examine the effectiveness of event notification on health outcomes for older adults who experience acute care events, and 2) compare approaches to how providers respond to event notifications.

**Methods:**

In a cluster randomized trial conducted across two medical centers within the U.S. Veterans Health Administration (VHA) system, we plan to enroll older patients (≥ 65 years of age) who utilize both VHA and non-VHA providers. Patients will be enrolled into one of three arms: 1) usual care; 2) event notifications only; or 3) event notifications plus a care transitions intervention. In the event notification arms, following a non-VHA acute care encounter, an HIE-based intervention will send an event notification to VHA providers. Patients in the event notification plus care transitions arm will also receive 30 days of care transition support from a social worker. The primary outcome measure is 90-day readmission rate. Secondary outcomes will be high risk medication discrepancies as well as care transitions processes within the VHA health system. Qualitative assessments of the intervention will inform VHA system-wide implementation.

**Discussion:**

While HIE has been evaluated in other contexts, little evidence exists on HIE-enabled event notification interventions. Furthermore, this trial offers the opportunity to examine the use of event notifications that trigger a care transitions intervention to further support coordination of care.

**Trial registration:**

ClinicalTrials.gov NCT02689076. “Regional Data Exchange to Improve Care for Veterans After Non-VA Hospitalization.” Registered 23 February 2016.

## Background

### Background and rationale

The U.S. healthcare system is characterized by high sub-specialization relative to international comparisons [1], creating significant need for coordination among the various types and levels of provider services. Patients receive care from a variety of providers, with some providers being outside of any one, organized network [2]. Moreover, individuals increasingly manage their health using a variety of interventions at home as well as the Internet [3]. Delivering high quality, coordinated care therefore requires that providers access, manage, and share information efficiently.

Managing a patient’s health information for care coordination activities, however, is challenging. In a study of internal medical residents, researchers observed that providers spent between 5 and 9% of their time looking for information on a patient [4]. In a survey of U.S. patients, 27% of respondents reported that during a medical visit their test results were either not available, or that duplicate tests were ordered; and 17% of patients reported that information was not shared among their multiple care providers [5]. Respondents from Australia, Canada, France, and other nations indicated similar information gaps with respect to care coordination [5].

To optimize care coordination, providers require health information technologies that facilitate access to information on their patients, regardless of its source. Health information exchange (HIE) is defined as the electronic transfer of clinical, administrative, or other information necessary for the delivery of health care across diverse systems or organizations [6]. Most often HIE takes the form of an information system transaction mediated by technical standards, such as the electronic reporting (or pushing) of a result from a laboratory information management system to an electronic health record (EHR) system using the Health Level Seven (HL7) messaging standard. Other times HIE involves querying (or pulling) information from another system, such as retrieval of the patient’s last radiological study performed by another provider using the Digital Imaging and Communications in Medicine (DICOM) standard.

Event notification is a form of HIE involving the electronic reporting (or pushing) of information pertaining to a clinical event from one provider to another facilitated by a messaging standard. Notification usually pertains to acute care events (e.g., hospitalization, emergency care), and the notifications are typically sent to primary care providers responsible for coordination of care [7]. To date, there has been one quantitative study of event notification sent to ambulatory providers for acute care events over a 3.5 year period using a regional HIE network [8]. The study found a statistically significant 2.9% reduction in 30-day readmissions observed during the intervention period. While promising, the evidence represents a single before-after cohort study. More research is necessary to establish robust evidence on the benefits of event notification services as a form of HIE for care coordination.

### Objectives

The objectives of this study are to 1) examine the effectiveness of event notification on health outcomes for older adults who experience acute care events, and 2) compare approaches to responding to event notification.

### Trial design

We will implement a multi-year, mixed methods study involving a clinical trial of the HIE intervention and qualitative examination of its implementation. A 2-site cluster-randomized trial will examine the impact of event notification introduced into multiple primary care medical homes part of a large integrated health system.

The trial involves three arms recruited in two phases as depicted in Fig. 1. In Phase 1, we will identify and enroll active subjects into one of two groups: 1) event notification only, in which the primary care provider is alerted when the subject has an acute care event outside the integrated health system; or 2) event notification plus geriatric care transitions intervention, in which the primary care provider is alerted in parallel with a geriatric care coordinator who will facilitate a standardized care transitions intervention for 30 days following discharge from the acute care facility. Assignment is based on the patient’s primary care medical home, which will be randomized to one of the arms. In Phase 2, we will retrospectively identify and capture data on a third group of concurrent control patients for which no notification or post-acute care transitions intervention was utilized. Comparisons will be performed between each intervention group and the control group as well as between the two intervention groups.

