### Sample size

Our sample size estimate is based on the primary outcome. Reports of randomized studies of geriatric care transitions interventions have reported 25–45% reductions in hospital readmissions [17, 20, 29]. Based on prior work as well as pilot data gathered within the VHA (unpublished), we postulate that the notification-only group as well as the usual care group will have a 40% readmission rate while the notification-plus-coordination group will have a 26% readmission rate in the 90-day post-discharge period (i.e., a clinically significant 35% reduction).

There are several features of the study that support this large potential effect. First, the targeted patients are at high risk of readmission because they are older veterans who utilize both VHA and non-VHA services, who have been shown in previous studies to have significantly higher readmission rates after acute illness. Second, in contrast to veterans hospitalized in the VHA who routinely receive PACT post-discharge telephone calls and follow-up, this group is naïve to any coordination intervention because PACT teams normally do not respond to non-VHA hospital encounters because they do not know about them. Thus, we postulate more than an incremental effect.

To account for possible dependence of the outcome among patients cared for by the same PACTs (clustering), we estimated the design effect [30] based on an average number of subjects per PACT = 7. Assuming the intraclass correlation is 0.05 (based on pilot data and prior literature [31]), we need to observe a total of 466 patients with non-VHA hospitalizations or ED visits (155 in the notification-plus-coordination group and 311 combined in the notification-only and usual care groups) to detect an effect size of 0.35 with 80% power and a two-tailed test at 5% significance. If the intraclass correlation is smaller (e.g., 0.04), which may be the case for a group of patients whose care is fragmented and perhaps less influenced by primary care team clustering, then the power will be higher.

In order to achieve the target sample size, we will enroll 300 patients at each site, with an estimated 25–30% of enrolled veterans experiencing non-VHA hospital encounters. We anticipate 10–15% attrition due to death or loss to follow up given the average age of veterans in the target population.

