### Statistical methods

All analyses will be performed as intention-to-treat (ITT), i.e. all outcomes will be included on patients assigned to treatment groups, even if they deviate from the group’s intervention. We will use a generalized linear mixed (GLM) model to test the effect on the primary outcome of 90-day hospital admission or readmission (e.g., 0 = no, 1 = yes). The logit link of the binary outcome for each observation will be modeled as a linear model, with the PACT team used as a random effect and group assignment (e.g., 0 = notification only or no notification, 1 = notification-plus-coordination) as a fixed effect. Inclusion of random effects in the model accounts for possible within-cluster correlation of the outcome since patients will be clustered by PACT.

To estimate the intervention effect after accounting for patient characteristics, especially those found to be imbalanced between study arms from the preliminary analyses, other covariates will be added as fixed effects to the model. These covariates may include: age, gender, non-VHA hospital, number of pre-admission medications, chronic illness count, discharge diagnosis, and length of stay for the index admission (with ED visits coded as 0 days). In addition to bias reduction, this analysis may increase the power for detecting the intervention effect by reducing the unexplained variance of the outcome and add insight into factors that predispose these patients to the outcome.

A similar approach will be used to test the intervention effect on secondary outcomes. For each secondary outcome, an appropriate distribution or link function will be chosen for the GLM model, e.g. logit link for the binary outcome of scheduled follow-up, Poisson or Negative Binomial distribution for the counts of high-risk medication discrepancies, identity or other links for Care Transitions Measure depending on the distribution of scores.

All analyses will be carried out using the most recent version of SAS (Carey, North Carolina, USA) available to VHA researchers using the VHA computing environment. For all tests, we will use 2-sided *p*-values with alpha = < 0.05 level of significance. Qualitative coding and analysis will be conducted using the most recent version of NVivo (QSR International; Doncaster, Victoria, Australia).

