## Discussion

Our study is innovative in its use of a trial design to examine the impact of event notifications, enabled by HIE, on health outcomes. HIE has been associated with a number of benefits [36], including a reduction in expensive imaging studies [37], improved population level immunization rates [38] and completeness of disease reporting to public health authorities [39]. Given the ability of HIE to facilitate access to patient information, especially after a handoff or transfer of care, there exists a strong theoretical case for HIE to impact care coordination activities [40], such as reintegration into primary care following an acute care episode. However, recent systematic reviews of HIE [36, 41] do not include such studies. This may be due to the fact that the only prior study examining event notification [8] utilized a cohort design found to be insufficient for inclusion in a systematic review. Our study is designed to generate high quality evidence on event notification, evidence needed for assessing the impact of HIE services on patient and population outcomes in future reviews.

Our study is further innovative in its combination of arms that enable examination of a care transitions intervention pioneered by Coleman et al. [16] beyond event notification enabled by HIE. Prior studies in multiple countries have examined interventions designed to improve care transitions for older adults [42–46], yet most focus on steps that can be taken by clinical staff within emergency department or hospitals prior to discharge. Few interventions can be implemented to initiate care transitions following discharge, because there are many breakdowns in communication with external primary care providers once the patient leaves a facility. The growth in HIE networks provides an opportunity to identify a discharge event and initiate timely follow up by primary care providers. This study is designed for sufficient power to examine not only the benefit of event notification but also the additional benefit of a care transitions intervention that can activate patients to better self-manage their complex disease and medication regimens at home.

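### Three pairwise comparisons are planned, but the primary model and sample size use one pooled contrast that cannot test the notification objective, and no contrast is named as deciding the trial

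*Protocol article*

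**What the plan says.** All references are to the protocol article.

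- **Objectives:** two aims. The first is the effect of event notification on health outcomes; the second compares ways of responding to notifications.
- **Trial design:** "Comparisons will be performed between each intervention group and the control group as well as between the two intervention groups". With arm 1 = notification only, arm 2 = notification plus coordination and arm 3 = control, the contrasts are 1 v 3, 2 v 3 and 2 v 1.
- **Statistical methods:** the mixed logistic model for 90-day admission or readmission has one binary term, "group assignment (e.g., 0 = notification only or no notification, 1 = notification-plus-coordination) as a fixed effect". This is 2 v (1 + 3).
- **Statistical methods, level:** "For all tests, we will use 2-sided *p*-values with alpha = < 0.05 level of significance".
- **Sample size:** the same pooled split, "155 in the notification-plus-coordination group and 311 combined in the notification-only and usual care groups". The calculation is for a single test at two-sided 5% with 80% power.
- **Discussion:** the study is said to have "sufficient power to examine not only the benefit of event notification but also the additional benefit of a care transitions intervention".

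**The concern.** The design section promises three comparisons, and the statistical section fits a model that delivers none of them. The binary term puts notification-only and no-notification patients in the same reference group, so the difference between them cannot be estimated from it. The first objective therefore has no test in the stated primary model, and the Discussion's power claim for notification has no calculation behind it.

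Two things are at stake. If several contrasts on the primary outcome can each support a claim at 5%, the chance of at least one false claim exceeds 5%. And if the contrasts disagree, the document gives no rule for what the trial concludes.

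**Working it through.** **1. What the sample size covers.** The postulates are "we postulate that the notification-only group as well as the usual care group will have a 40% readmission rate" and "the notification-plus-coordination group will have a 26% readmission rate in the 90-day post-discharge period". The relative reduction is (0.40 − 0.26)/0.40 = 0.35, as stated. With 7 patients per PACT and ICC 0.05, the design effect is 1 + (7 − 1) × 0.05 = 1.30. The usual two-proportion formula at 1:2 allocation gives 134 + 268 = 402 patients, and 402 × 1.30 ≈ 523, not the stated 466. Power at 155 v 311 is about 75%. That mismatch is a separate matter and does not affect this point. What matters here is that the calculation covers one contrast at one 5% level, and that it sets arms 1 and 3 to the same 40%. It thus assumes no effect of notification alone, and cannot show power to detect one.

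**2. Familywise error if any significant contrast counts.** Assumptions: primary outcome only, equal true rates in all three arms, each test at |z| > 1.96. Arm 2 is held at 155 and arms 1 + 3 at 311. The article does not divide the 311, so the split is varied. Three independent normal arm means with variances proportional to 1/n were simulated (4 million draws). The contrasts are m₁ − m₃, m₂ − m₃, m₂ − m₁ and m₂ − (n₁m₁ + n₃m₃)/(n₁ + n₃), each divided by its standard error.

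| Arms 1 / 2 / 3 | Three pairwise | Plus pooled contrast |
|---|---|---|
| 155 / 155 / 156 | 12.2% | 12.8% |
| 200 / 155 / 111 | 12.2% | 12.8% |
| 100 / 155 / 211 | 12.1% | 12.7% |
| 75 / 155 / 236 | 12.0% | 12.6% |

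Analytic check for equal arms: the probability that the studentised range of three means exceeds 1.96 × √2 = 2.77 is 0.122, which agrees.

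Letting control patients share PACTs with the intervention arms (ICC 0.05, several arm sizes) gave 11.8-12.2% and 11.9-12.8%. Treating the tests as independent would give 1 − 0.95³ = 14.3% or 1 − 0.95⁴ = 18.5%. Both overstate the error, because the contrasts are correlated.

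**3. Can the contrasts disagree?** Take 155/155/156 patients in arms 2/1/3, illustrative observed rates of 30%, 36% and 43%, and design effect 1.30. SE = √{1.30 × [p(1 − p)/n + q(1 − q)/m]}. The pooled reference rate is (155 × 0.36 + 156 × 0.43)/311 = 0.395.

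| Contrast | Difference | SE | z | p |
|---|---|---|---|---|
| 2 v 3 | 0.130 | 0.0617 | 2.11 | 0.035 |
| 2 v (1 + 3) | 0.095 | 0.0525 | 1.81 | 0.07 |
| 2 v 1 | 0.060 | 0.0608 | 0.99 | 0.32 |

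The same data give success on one contrast and failure on the other two.

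**The case against.** **A primary contrast is identifiable.** The Sample size and Statistical methods sections agree on the pooled contrast, and if it alone decides, its error is 5%. This largely stands: the pooled contrast is the implied primary. But the article never says so, and under that reading the first objective has no primary test while the Discussion still claims power for it.

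**Multiplicity rules belong in the analysis plan, which is not shown.** This also stands as far as it goes. The lack of a hierarchy in a condensed article would not be a finding on its own, and the 5% is stated per test, with no claim of familywise control. What remains is in the text itself: a three-comparison plan, a one-term model that cannot deliver it, and a claim about notification that the model cannot support.

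**The 12-13% is conditional.** It requires equal true rates in all three arms. Under the article's own postulate (40%, 40%, 26%) only 1 v 3 is a true null, and the error among the pairwise tests is 5%. The same holds whenever exactly one arm differs from two equal ones. This is correct.

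**The use of *e.g.* before the group coding.** A reader might infer that it leaves the primary contrast open. The same section uses *e.g.* for the 0/1 coding of the binary outcome, where no alternative is meant, so the wording does not show that.

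**Conclusion.** The point holds as an unreconciled plan. Three pairwise comparisons are promised, one pooled contrast is modelled and sized, and the pooled contrast can neither test the first objective nor support the Discussion's claim about notification. Which contrast decides the trial is not stated.

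A reader might go further and infer that the trial as written carries a 12-13% false-positive risk. The document does not support that unconditionally. The figure applies to the primary outcome alone, when no arm truly differs and any one significant contrast may be claimed as success. The possibility of conflicting contrasts does not depend on those conditions; the rates in that example are illustrative, and its equal split of the 311 is an assumption.

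**What to change.** In Statistical methods:

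1. Name one contrast on 90-day admission or readmission as the deciding test at two-sided 5%.
2. Fit group as a three-level factor, so that the comparisons in Trial design can be estimated. If the pooled contrast is the deciding one, define it as a contrast of that factor with weights stated in advance.
3. Test the remaining contrasts in a pre-stated fixed order at 5%, each only if the one before is significant. Report estimates and 95% confidence intervals for all of them regardless.
4. Choose the order with the first objective in mind, and bring the Discussion's power claim into line with it. Only 2 v 1 compares randomised groups, since arm 3 is identified retrospectively; that also bears on the choice.

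Cost: a few sentences, and the deciding test keeps its full 5%. A contrast late in the order cannot be claimed as confirmatory when an earlier one fails; that includes notification-only v control if it is placed last. Keeping the pooled contrast as the deciding test leaves the planned numbers as they are. Choosing another changes the power: 2 v 1 with 155 per arm (an assumed split), 26% v 40% and design effect 1.30 has about 63%.

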**Fig. 1 Fig1:**
[figure not shown]
Overview of the study population, study arms, and phases of the study. VA = Veterans Affairs

In addition to the quantitative trial, we will further perform a qualitative assessment examining the implementation of event notification as well as the care transitions intervention. This component of the study will examine the facilitators and barriers of the HIE-based intervention as well as care coordination following the transition of care. Interviews with providers and patients will elicit details about socio-technical dimensions that cannot be measured quantitatively using data from the trial.

## Methods

### Study setting

The study takes place in the context of the Veterans Health Administration (VHA). The VHA is the largest integrated health care system in the United States, providing care at 1,243 health care facilities, including more than 170 medical centers and 1,000 outpatient clinics, serving 9 million enrolled veterans each year.

The VHA has a need to improve care coordination between VHA-based providers and non-VHA providers who practice in community hospitals, private clinics, and other networks such as federally qualified health centers. In a survey of non-VHA providers part of a practice-based research network [9], respondents reported poor communication with VHA colleagues, and their interactions were perceived to be with a “system” rather than a colleague. Moreover, VHA is under pressure to provide more non-VHA care to Veterans in an effort to improve access to care following a series of appointment scheduling challenges [10].

Historically the VHA spent around 10% of its total health care dollars on care delivered to veterans outside of the VHA’s network of providers [10]. Recent legislation-- the CHOICE Act of 2014 [11] and MISSION Act of 2018 [12] -- directs the VHA to expand out-of-network care to veterans. Since the passage of the CHOICE Act, the VHA has authorized nearly 6 million non-VHA visits for nearly 2.4 million unique Veterans, nearly one-third its total population. As non-VHA care visits increase, VHA needs to strengthen care coordination processes to control quality as well as costs.

Two medical centers within the VHA are included in the study. The first medical center is the James J. Peters VA Medical Center (JJP VAMC) located in the Bronx, New York. The JJP VAMC cares for more than 26,000 patients annually via a tertiary care facility providing comprehensive inpatient as well as outpatient care services in addition to four community-based outpatient clinics. The second medical center is the Richard L. Roudebush VA Medical Center (RLR VAMC) located in Indianapolis, Indiana. The RLR VAMC serves more than 62,000 patients annually and consists of a tertiary care facility providing comprehensive inpatient as well as outpatient care services in addition to three community-based outpatient clinics. Both medical centers also serve as teaching hospitals and regional referral sites.

The study utilizes cluster randomization in which the interventions will be randomly allocated to the primary care teams distributed across the two sites. Roughly half of the primary care teams at each site will be randomly assigned to the event notification-only arm. The other half will be allocated to the event notification plus geriatric care transitions intervention. Clustering within primary care teams prevents bias with respect to providers who might, once they become aware that some patients are receiving a care transitions intervention, try to emulate that service for other patients who may be allocated to a notification-only arm.

